## Abstract

**Background:**

Robot-assisted gait training (RAGT) was developed to restore gait function by promoting neuroplasticity through repetitive locomotor training and has been utilized in gait training. However, contradictory outcomes of RAGT have been reported for patients with Parkinson’s disease (PD). In addition, the mechanism of the RAGT treatment effect is still unknown. This study aims to investigate the effects of RAGT on gait velocity in patients with PD and to unveil the mechanisms of these effects.

**Methods:**

This is a prospective, single-blind, single-center, randomized controlled trial. Eligible participants will be randomly allocated to: 1) a Walkbot-S™ RAGT group or 2) a treadmill training group. The participants will receive three 45-min sessions of each intervention per week for 4 weeks. Gait speed during RAGT will be targeted to the maximal speed depending on the participant’s height; the same principle will be applied to the treadmill training group to match the training intensity. The primary outcome measure is gait speed measured by the 10-Meter Walk Test at a comfortable pace under single-task conditions. Secondary outcomes include dual-task interference, the Berg Balance Scale, Timed Up and Go test, the Korean version of the Falls Efficacy Scale-International, New Freezing of Gait Questionnaire, Movement Disorder Society-sponsored revision of the Unified Parkinson’s Disease Rating Scale, and functional connectivity measured by resting-state functional magnetic resonance imaging. Baseline assessments (T0) will be conducted to acquire clinical characteristics and outcome measure values before the intervention. Postintervention assessments (T1) will compare immediate efficacies within 3 days after the intervention. Follow-up assessments (T2) will be conducted 1 month after the intervention. Considering an alpha of 0.05 and a power of 80%, the total number of participants to be recruited is 44.

**Discussion:**

This study will reveal the effect of RAGT using an exoskeletal robot, not only on gait speed, but also on gait automaticity, balance function, fall risk, quality of life, and disease severity. In addition, the study will shed new light on the mechanism of the RAGT effect by evaluating changes in gait automaticity and brain functional networks.

**Trial registration:**

ClinicalTrials.gov, NCT03490578. Registered on 21 March 2018.

**Electronic supplementary material:**

The online version of this article (10.1186/s13063-018-3123-4) contains supplementary material, which is available to authorized users.

## Background

Robot-assisted gait training (RAGT) was developed to restore gait function by promoting neuroplasticity through repetitive locomotor training [1]. Exoskeletal and end-effector robots have been commercialized and utilized in gait rehabilitation [2]. In the area of brain diseases, most clinical studies have been conducted on stroke patients. According to a recent systematic review, machine- and robot-assisted gait training improved walking independency in subacute stroke patients who could not walk by themselves [3]. The American Heart Association/American Stroke Association (AHA/ASA) guideline for adult stroke rehabilitation recommended RAGT to improve motor function and mobility with a class IIb level of evidence A [4]. However, there is still a lack of studies of RAGT in brain diseases other than stroke, and clear guidelines are not provided.

Parkinson’s disease (PD) is a neurodegenerative disorder presenting with resting tremor, rigidity, bradykinesia, postural instability, and gait disturbance. Gait disturbance is one of the most disabling symptoms of PD [5]. Reduced step height, short stride, slow gait, and freezing of gait are common gait problems in patients with PD. Although pharmacological treatment has been the mainstay of PD management, most patients experience functional aggravation despite optimal medication [6]. Deep brain stimulation, a surgical intervention to treat PD, has become an acceptable treatment option. However, because of the risks and complications of the procedure, it has been limited to some advanced patients with medically refractory symptoms [7]. So far, no cure for PD has been developed. Therefore, rehabilitation has been an essential element in maintaining the maximum level of mobility and independence in patients with PD. For gait rehabilitation in PD, treadmill training has been a common approach. Thus, conventional treadmill training was selected as a comparator in this study protocol.

A major impairment causing gait disturbance in PD is the hypokinesia of gait [8]. Gait hypokinesia is associated with reduced stride length and step height, decreased cadence, and prolonged double limb support. It is one of the most disturbing symptoms affecting quality of life in PD [9] and can be quantified as the gait velocity. Decreased gait automaticity is another important cause of gait disturbance in PD [10]. Once a skilled movement has been learned, the movement becomes automatic and does not require much conscious endeavor or attention. Gait automaticity refers to the ability to walk without cognitive effort or attention [11]. In patients with PD, loss of dopamine in the sensorimotor territories of the basal ganglia disturbs habitual control [12], so that gait automaticity is decreased and patients have to rely on attentional resources or make a conscious effort to walk. Dual-task performance demands greater attentional cost and cognitive effort, and therefore gait automaticity can be quantified as the dual-task interference. For these reasons, this study will focus on the change in gait velocity and dual-task interference between before and after the intervention.

There are studies of the effects of RAGT on gait velocity with better outcomes for RAGT than the control group [13–16], as well as insignificant outcomes [17–19]. Some studies on PD have suggested that RAGT might improve freezing of gait, postural instability, and gait performance [13–16, 20]; however, several studies have reported that RAGT is not superior to conventional therapy for improving postural instability and gait performance [17, 18, 21]. Due to the contradictory results, a well-designed study is needed to clarify the effect of RAGT on gait function in PD. Impaired automaticity leads to gait disturbance and falls in PD, especially in situations when the patients conduct secondary tasks in parallel with gait. So far, there are no studies that have investigated the effect of RAGT on gait automaticity in PD; therefore, a further study is needed to reveal this effect.

There appears to be an association between brain networks and gait function in PD. Functional connectivity has been reported to be decreased even in the early stages of PD [22, 23], and freezing of gait might be a consequence of alterations in brain functional networks [24, 25]. RAGT was suggested to improve gait recovery by promoting brain plasticity [26]. Therefore, there is a need to study changes in functional connectivity after RAGT in PD. In this study, resting-state functional magnetic resonance imaging (MRI) will be conducted to discover significant changes in functional connectivity and compare the functional networks of the brain before and after the intervention.

The primary objective of this study is the verification of the hypothesis that RAGT can produce greater improvement, compared with conventional treadmill training, in gait speed at a comfortable pace. Secondarily, this study aims to determine whether gait automaticity, balance, mobility, fall risk, and disease severity are improved by RAGT. Thirdly, this trial will shed new light on the mechanism of the RAGT treatment effect by investigating dual-task interference and functional connectivity before and after the intervention.

## Methods

### Trial design

This is a prospective, single-blind (assessors), single-center, randomized controlled trial. Eligible participants will be randomly allocated to: 1) a RAGT group or 2) a treadmill training group. Figure 1 shows the Consolidated Standards of Reporting Trials (CONSORT) flow diagram for this study. Baseline assessments (T0) will be conducted to acquire clinical characteristics and values of the primary and secondary outcome measures before the intervention. Postintervention assessments (T1) to compare the immediate efficacy between the two groups will be performed within 3 days after the intervention. Follow-up assessments (T2) will be conducted 1 month after the intervention. All procedures have been approved by the Institutional Review Board of the Seoul National University Hospital in accordance with good clinical practices, the Helsinki Declaration, and national regulations. The clinical trial was also approved by the Korean Ministry of Food and Drug Safety.

**Fig. 1 Fig1:**
[figure not shown]
Consolidated Standards of Reporting Trials (CONSORT) flow diagram

### Sample size

The primary outcome measure in this study is gait speed in postintervention assessments measured by the 10-m walk test (10MWT) at a comfortable pace under single-task conditions. Previous studies, in which similar populations and intervention protocols were employed, have reported that the minimal detectable change in comfortable gait speed measured by the 10MWT was 0.18 m/s [27] and the standard deviation was 0.08–0.20 m/s [13, 17]. Based on those findings, we consider 0.18 m/s as a clinically significant improvement in gait speed and 0.20 m/s as an acceptable standard deviation. Consequently, 20 participants per group will be required to achieve 80% power with a two-tailed α of 0.05, as determined by [28]:$$ N=\frac{2{SD}^2{\left({Z}_{\alpha }+{Z}_{\beta}\right)}^2}{\triangle^2} $$

With an expected drop-out rate of 10%, a total of 44 participants should be recruited, 22 for each group, to establish the relative efficacy of each intervention in improving gait velocity.

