### Statistical analysis

Data will be analyzed using the Statistical Package for the Social Sciences (SPSS) version 20. Statistical significance will be accepted when a *p* value is less than 0.05. The intention-to-treat (ITT) principle will be adopted in all analyses. All participants randomized to a group will remain in the group regardless of protocol violations or dropout. Last observation carried forward (LOCF) will be used to impute missing values. Per-protocol analyses will also be conducted. All participants from the ITT population without serious protocol violations will be included in the per-protocol population. Serious violations include exceptions to eligibility criteria and deviations from the treatment scheme such as not completing at least eight of the total of 12 sessions.

For the primary outcome analysis, the change between T0 and T1 in gait speed at a comfortable pace under single-task conditions will be analyzed using Student’s *t* test. Generalized estimating equation (GEE) models will be employed to identify differential changes of secondary outcome measures across multiple time points.

Functional connectivity in the whole brain area will be analyzed using the primary motor cortex as a seed region. Pearson’s correlation coefficient will be used to calculate functional connectivity. Comparisons of functional connectivity will be conducted using two sample *t* tests for between-group differences and paired *t* tests for within-group effects.

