## Discussion

Robots have been increasingly used for gait rehabilitation, especially in patients with brain diseases such as stroke and multiple sclerosis [43, 44]. However, contradictory results have been reported by studies of RAGT in patients with PD. In addition, there are no clinical guidelines for RAGT in gait training for PD. Moreover, even in studies reporting gait improvement by RAGT in PD, the mechanism of the treatment effect remains elusive.

RAGT in this study will include a visual feedback and an auditory cue, which are known as effective strategies to treat locomotor impairments [45]. Feedback or cues were reported to improve gait performance in patients with PD [46], and an additional beneficial effect of cues with gait training has been suggested [47]. External cues appear to help patients with PD walk better by compensating for the impaired central drive for walking [48]. Another hypothesis is that external cues enable patients to utilize the intact premotor cortex, rather than the impaired basal ganglia/supplementary motor area circuit [49]. Therefore, RAGT including external cues or feedback is expected to improve gait performance in patients with PD.

This study will reveal the effect of RAGT using an exoskeletal robot, not only on comfortable gait speed, but also on dual-task interference, balance function, fall risk, and disease severity. In addition, the findings of the study will provide knowledge on the recovery of gait automaticity and brain functional connectivity following RAGT. We hope that the information acquired from this trial will advance our understanding of the mechanism of the RAGT treatment effect and improve clinical decision making when physiatrists consider gait training for patients with PD.

A limitation of this study is that it involves only one center. This might influence the generalizability of the results to other centers. Another limitation is that blinding of patients and therapists is not possible due to the definite different feature of the interventions.

In summary, this trial will compare the effects of RAGT with those of treadmill training on gait performance in patients with PD. The results of this study will provide clear evidence whether RAGT rather than treadmill training may be recommended for gait training in patients with PD.

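### The stated 80% power is for 20 completers per group, not for the planned ITT analysis with LOCF, where it is about 75–77% if all dropout precedes T1 and 0.20 m/s is the SD of change

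*Protocol article*

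**What the plan says.** - **Sample size.** The target is 0.18 m/s with an SD of 0.20 m/s: "we consider 0.18 m/s as a clinically significant improvement in gait speed and 0.20 m/s as an acceptable standard deviation". From these the section concludes that "20 participants per group will be required to achieve 80% power with a two-tailed α of 0.05". It then allows for loss: "With an expected drop-out rate of 10%, a total of 44 participants should be recruited, 22 for each group".
- **Abstract, Methods.** The same power is attached to the recruited total: "Considering an alpha of 0.05 and a power of 80%, the total number of participants to be recruited is 44".
- **Statistical analysis.** Every randomised participant stays in the assigned group whatever happens later, and "Last observation carried forward (LOCF) will be used to impute missing values". The primary test is Student's t test on the change in comfortable gait speed from T0 to T1.
- **Trial design.** The assessments are T0 (before the intervention), T1 (within 3 days after it) and T2 (1 month after it). No assessment lies between T0 and T1.
- **The SD.** The Sample size section describes the outcome as gait speed at the post-intervention assessment and takes 0.20 m/s from a reported range of 0.08–0.20 m/s. It does not say whether these are SDs of speed at one visit or of change.

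**The concern.** The sample size and the primary analysis treat dropouts differently. Adding two people per group for 10% loss assumes that dropouts disappear and that about 20 completers per group show the full 0.18 m/s. Under ITT with LOCF they do not disappear. A participant without T1 has only T0 to carry forward, so the imputed change is exactly zero in either group. Zeros in both groups shrink the difference that the t test sees, and the extra two per group do not fully make up for it.

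At stake is whether the advertised power belongs to the analysis that will be reported. The undefined SD adds to this, because the test is on change and the power depends heavily on which SD was meant.

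**Working it through.** **Inputs.** From Sample size: difference 0.18 m/s, SD 0.20 m/s, two-sided α 0.05, dropout 10%, 22 per group. From Statistical analysis: t test on T0–T1 change, ITT, LOCF. Not in the protocol and therefore assumed: when dropout occurs, the mean change on treadmill, and that 0.20 m/s is the SD of change among those observed.

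**1. The protocol's own figure.** n = 2 × 0.20² × (1.960 + 0.842)² / 0.18² = 19.38, so 20 per group. The t-test power with 20 completers per group is 79.2% (noncentrality 0.18 / (0.20 × √(2/20)) = 2.85, 38 df). This agrees with the stated 80% for practical purposes.

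**2. The planned analysis.** Let a fraction d = 0.10 of each group have change 0.
- Tested difference: (1 − 0.10) × 0.18 = 0.162 m/s.
- Variance in a group with mean change μ among those observed: (1 − d) × 0.20² + d(1 − d) × μ² = 0.036 + 0.09μ².
- Pooled SD: the root of the mean of the two group variances, with the RAGT mean equal to the treadmill mean + 0.18.
- Noncentrality: 0.162 / (pooled SD × √(2/22)), with 42 df.

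| Treadmill mean change (m/s) | Group variances (treadmill, RAGT) | Pooled SD | Noncentrality | Power |
|---|---|---|---|---|
| 0 | 0.0360, 0.0389 | 0.194 | 2.78 | 77.4% |
| 0.10 | 0.0369, 0.0431 | 0.200 | 2.69 | 74.7% |
| 0.20 | 0.0396, 0.0490 | 0.210 | 2.55 | 70.3% |

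Simulation of the same analysis (100,000 trials per setting) gives 77.8%, 74.6% and 70.0%.

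**3. How far this depends on the assumptions** (22 per group, treadmill change 0 to 0.10 m/s).
- Only 5% leave before T1 and SD is 0.20: 80.3% to 79.0%.
- 10% leave before T1 and the change SD is 0.18: 85% to 82%.
- With the difference fixed at 0.162 m/s, power reaches 80% once the SD entering the test is about 0.187 or less.

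**4. If 0.20 m/s is the SD at a visit.** Assuming equal SDs at T0 and T1, the SD of change is 0.20 × √(2(1 − ρ)). With 20 completers per group and no LOCF dilution:

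| T0–T1 correlation ρ | SD of change | Power |
|---|---|---|
| 0.3 | 0.237 | 65% |
| 0.5 | 0.200 | 79% |
| 0.7 | 0.155 | 95% |

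The two readings of 0.20 m/s coincide only at ρ = 0.5, and the protocol gives no correlation.

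**5. Alternative analysis.** Simulated ANCOVA on observed T1 data, with baseline as covariate, 22 per group, 10% missing at random and change SD 0.20, gives about 87%, 84% and 82% at ρ = 0.5, 0.7 and 0.8. These figures are good to about one percentage point.

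**The case against.** The strongest reply is that the quoted sentence is right. It claims 80% power for 20 per group by the printed formula, and the formula delivers that. A reader might infer an arithmetic error, but there is none. The gap between normal and t-based power, and the choice of 22 rather than 23 per group, are too small to matter.

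The second reply is that 75–77% needs inputs the protocol does not supply: all dropout before T1, a treadmill change between 0 and 0.10 m/s, and a change SD of exactly 0.20. Follow-up runs to T2, so part of the 10% may leave after T1. The SD was also taken from the top of the reported range. This stands, and it makes the shortfall conditional. It does not remove the mismatch, because the sample size allows for dropouts as exclusions while the analysis counts them as zeros.

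Two stronger readings are tempting.
- A reader might infer that 0.18 m/s is invalid as a target because it is introduced as a minimal detectable change. The protocol discloses that origin and presents the choice as its own judgement ("we consider 0.18 m/s as a clinically significant improvement in gait speed"). The relabelling can fairly be questioned, but nothing in the document shows another value to be right.
- A reader might infer from the Discussion's promise that the trial "will provide clear evidence whether RAGT rather than treadmill training may be recommended" that a null result will count against RAGT. That is a closing sentence, not a decision rule, and the point does not rest on it.

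**Conclusion.** The point holds in a limited form. The 80% in the Abstract and the Sample size section belongs to 20 completers per group, not to the ITT analysis with LOCF. If all 10% leave before T1 and 0.20 m/s is the SD of change, power is about 75–77% for a treadmill change of 0 to 0.10 m/s, and 70% at 0.20 m/s. Over the 0 to 0.10 m/s range that is 3 to 5 points below the stated figure. It largely vanishes if only half the dropout precedes T1, and a somewhat smaller change SD also restores 80%.

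The unstated meaning of the SD is the larger uncertainty and can move power in either direction. A reader might infer that the trial is materially underpowered and must enrol more. The document does not support that.

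**What to change.** Do not enrol more participants.

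1. **Preferred.** In the primary analysis, replace LOCF with a baseline-adjusted analysis of observed T1 data (ANCOVA or a mixed model), with participants analysed as randomised. Power is then roughly 82–87% at 10% dropout, for assumed correlations of 0.8 down to 0.5 and change SD 0.20. The cost is a change to the primary analysis, to be made before unblinding, and an explicit assumption that missingness is random given baseline.
2. **If LOCF is kept.** Restate the power as about 75–77% in the Abstract and the Sample size section, together with the assumptions on dropout timing, treadmill change and SD. The cost is wording and a slightly less favourable figure.
3. **In either case.** State that 0.20 m/s refers to the SD of change, if that is what was meant, and that 0.18 m/s is an assumed between-group difference. Report the difference with its 95% CI, so that a non-significant result is not read as evidence of no benefit. The cost is wording only.

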### Participants

In total, 44 participants will be recruited from the Department of Rehabilitation of the Seoul National University Hospital (Seoul, Republic of Korea). Approved trial posters including the inclusion, exclusion criteria, and contact details of researchers will be displayed in appropriate clinics.

The inclusion criteria are:Clinically diagnosed as idiopathic PDMen or women aged ≥ 18 yearsHoehn-Yahr stage 2.5 or 3Mini-Mental State Examination (MMSE) score ≥ 24

The exclusion criteria include:Severe dyskinesia or severe on-off phenomenonPlan to adjust medication at the time of screeningSensory dysfunction in lower extremitiesVestibular disease or benign paroxysmal positional vertigoSevere medical problems such as cardiovascular diseasesOther neurological or orthopedic disorders affecting lower extremities

Participants will be individually consented to participate in the entire study. The Principal Investigator and clinical research coordinator will obtain the written informed consent from all participants.

### Randomization and blinding

Randomization and allocation will be performed using computer-generated block randomization with a block size of 4 and 6. An independent researcher who is not in contact with any patient will perform the randomized allocation. The ratio between the RAGT and treadmill training groups will be 1:1. Details of the allocated group will be given in sequentially numbered, opaque, sealed envelopes to the research assistants in sequential order. The principal investigator, outcome assessors, and data analysts will be blinded to the group allocations of the participants until statistical analysis.

### Interventions

Participants in the RAGT group will receive gait training with the Walkbot-S™ (P&S Mechanics, Seoul, Korea) for 12 sessions (Fig. 2). Training is preceded by fitting and adapting the equipment to the participant. In the first training session, RAGT starts at the reference velocity depending on the participant’s height (Table 1) and reaches 80% of the maximal velocity at the end. Starting with the third training session, the initial gait velocity is increased and the final velocity becomes the maximal velocity depending on the participant’s height. Starting with the seventh training session, training velocity reaches the maximal velocity after 10 min. Table 2 shows an example of a training protocol for a participant whose height is 160 cm.

